**Fig. 2 Fig2:**
[figure not shown]
SPIRIT Flow chart. The red star marks the cross-over option for the CMM group. *TNS: Trial stimulation phase (1 week)

Total study duration is anticipated to be 2 years.

### Sample size

Sample size estimation is based on a ‘responder’ analysis as recommended by the Initiative on Methods, Measurement, and Pain Assessment in Clinical Trials (IMMPACT) group recommendations [14]. The estimated proportion of responders (≥ 50% reduction in pain NPRS) in the CMM group is 10%, based upon data generated by a RCT on SCS in failed back surgery syndrome (FBSS) [15]. Expected effect size in the Axium® group is extrapolated from published literature [11, 12]. The targeted effect size is a difference in proportion responding to treatment (Axium® vs. CMM) at the 6-month time point of 40%; i.e., 50% responding in Axium® group vs. 10% in the CMM group. With 90% power and 2p = 0.05, using a normal approximation with continuity correction, 31 subjects are required in each group at the 6 months primary endpoint analysis follow up point. With an allowance for attrition of 20% in both arms at 6-month follow-up, a total of 78 subjects is recruited (62/0.8 = 78). Sample size estimation was conducted using Stata software (version 13.1; StataCorp, College Station, TX). Figures were verified using Medcalc® software (v.14.8). There are no specific data to judge the effect size of CMM or the drop out rates in this specific study population.

### Statistical analysis

The primary analysis is a comparison of the proportion of responders (≥ 50% pain relief) in the Axium® versus CMM group at the 6-months time point. The mean difference between proportions and 95% confidence intervals are calculated. A risk difference is obtained using generalized linear modeling with a binomial distribution and an identity link. Difference between groups in the change in pain score (6-months minus baseline), adjusted for any chance imbalance between groups at baseline (ANCOVA model) are also calculated. The mean treatment effect (Axium® minus CMM) together with its 95% confidence interval is obtained. NNT will also be calculated as the reciprocal of the difference in proportions of responders (Axium® minus CMM) and presented with its 95% confidence interval. All analyses are conducted both ‘as randomized’ (intention to treat principle) and ‘as treated’ (secondary).

## Discussion

The results of the presently proposed ´SMASHING´ trial may shed light on a possible viable alternative treatment option once other treatments have failed in therapy resistant patients with PSIP. A very recent consensus protocol does not address this group [6]. Based on a retrospective analysis of 10 CPIP patients who were implanted with DRG stimulation leads, the technique is very promising. Eight of these 10 patients reported > 50% pain relief whereas a 77% mean VAS reduction was attained. [11] However, it is obvious that a proper RCT is required using a cross-over design. Firstly, a placebo controlled setting is inappropriate as it is clearly noticeable for patients if a sham device is implanted because of the absence of paresthesia. Secondly, ethics direct that the control group is not to be denied access to the therapy for which a cross-over is offered. Thirdly, a control group is heterogeneous because of the often individually tailored treatments for these therapy-resistant patients. This heterogeneity however mirrors daily clinical practice, and therefore generalization of the forthcoming results will be realistic. Moreover, possible confounding variables are controlled with randomization. The PROCESS study used a similar construction [15].

It must be appreciated that the validation of various outcomes is of utmost importance in pain treatment studies. Pain reduction scores are subjective whereas the clinical relevance of a 30% or 50% pain reduction is debatable. The presently proposed outcome measurements are linked to improved patient satisfaction, diminished medication usage, daily functioning and sleeping quality and a positive expert’s opinion regarding patient’s improvement [16–19]. We will address these components as well as other secondary outcomes as all of these issues are indispensable for a thorough efficacy analysis of any type of novel pain treatment.

### Update

Per 17-Jan-2017, sponsorship of the study has been transferred from St. Jude / Abbott to the Maxima Medical Center and primary investigator due to a slow inclusion rate. Analysis of the preliminary results of 18 patients enrolled from March 2015 to November 2016 is currently performed using repeated measures ANOVA on the primary outcome (number of patients with > 50% pain reduction and individual pain reduction). The original protocol did not describe regulations for interim analysis, but the authors will adhere to Bayesian approach as described in Li and Gates, 2013 [20].

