### Study endpoints

The primary outcome is percentage of subjects experiencing a minimal 50% reduction in average daily pain intensity as measured using the average NPRS as noted in pain diaries in the Axium® group as compared to the CMM group. Group differences in the change in pain intensity scores (NPRS) at the 6-month FU visit are also calculated. The analysis will be done following an Intention to Treat (ITT) principle.

Secondary outcomes are an ‘as treated’ analysis of the percentage of subjects experiencing a minimal 50% reduction in average daily pain intensity (NPRS) at 6 months and the mean difference in the change in pain intensity scores (NPRS) between the successfully trialed subjects with the Axium® arm as opposed to the CMM arm. This ‘as treated’ analysis is important as it reflects clinical convention i.e. utilization of a therapy trial (TNS) to improve changes of a successful outcome with the fully implantable system. A number needed to treat (NNT) analysis at the 6-months time point for ≥30% and ≥50% pain relief is also performed. However, reduction in pain intensity is not the only clinically relevant outcome in chronic pain patients. Changes in disability, pain interference, neuropathic pain symptoms, sleeping disorders and health resources utilization are also investigated using validated questionnaires at baseline and each follow-up visit. (Fig. 2).

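### The Update's preliminary analysis applies repeated measures ANOVA to a two-part primary outcome with no time point, which conflicts with the planned 6-month responder risk difference

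*Protocol article*

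**What the plan says.** Study endpoints defines a single responder outcome: "The primary outcome is percentage of subjects experiencing a minimal 50% reduction in average daily pain intensity", Axium against CMM, by intention to treat. The same paragraph then adds the continuous score: "Group differences in the change in pain intensity scores (NPRS) at the 6-month FU visit are also calculated".

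Statistical analysis gives the time point and the models. For the responder outcome it says: "The primary analysis is a comparison of the proportion of responders (≥ 50% pain relief) in the Axium® versus CMM group at the 6-months time". The model for that comparison follows: "A risk difference is obtained using generalized linear modeling with a binomial distribution and an identity link". For the change in pain score from baseline to 6 months, the group difference is "adjusted for any chance imbalance between groups at baseline (ANCOVA model").

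Sample size is built on the same responder comparison, 50% against 10% at 6 months.

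The Update describes "Analysis of the preliminary results of 18 patients enrolled from March 2015 to November 2016". On method, it says that this work "is currently performed using repeated measures ANOVA on the primary outcome (number of patients with > 50% pain reduction and individual pain reduction"). It names no visit and no contrast. Its next sentence admits that the original protocol had no rules for an interim analysis and commits the authors to a Bayesian approach. It does not say how that fits with the ANOVA.

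**The concern.** The Update and the Methods are both current text, and they describe the primary outcome differently in four respects: the model, the number of quantities, the cut-off and the time point. No reason is given for any of them.

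The model matters most. ANOVA assumes roughly normal residuals with equal variance, and a responder indicator in a handful of patients has neither. A p-value from it cannot be read at its nominal level, and the output is not the risk difference that the plan promises.

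The setting adds to this. It is an unplanned look at efficacy data, taken while sponsorship changed hands because inclusion was slow. With an ANOVA in one sentence and a Bayesian approach in the next, a reader cannot tell which analysis of which outcome will be presented as the preliminary primary result.

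**Working it through.** **Inputs.** Responder rates 50% and 10%, two-sided 0.05, 90% power, continuity correction, 31 per arm, 20% attrition, 78 in total (Sample size). Allocation 1:1 (Randomization). 18 patients (Update). The split of the 18 by arm is not stated; 9 per arm is my assumption.

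**1. The two descriptions side by side.**

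| | Study endpoints and Statistical analysis | Update |
|---|---|---|
| Primary outcome | one: responder yes/no | two: responder count and individual pain reduction |
| Cut-off | ≥50% | >50% |
| Time point | 6 months | none |
| Model, responders | binomial GLM, identity link | repeated measures ANOVA |
| Model, pain change | ANCOVA, as an additional analysis | repeated measures ANOVA |

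**2. The plan's own figure.** Without correction:

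n = [1.960·√(2·0.3·0.7) + 1.282·√(0.5·0.5 + 0.1·0.9)]² / 0.4² = (1.270 + 0.747)² / 0.16 = 25.4

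With continuity correction: (25.4/4)·[1 + √(1 + 4/(25.4·0.4))]² = 30.2, so 31 per arm. Then 62/0.8 = 77.5, so 78. Both stated figures reproduce. The trial was therefore sized for a comparison of two proportions.

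**3. Variances.** A 0/1 outcome has variance p(1 − p): 0.5·0.5 = 0.25 for Axium and 0.1·0.9 = 0.09 for CMM, a ratio of 2.8. If the treatment works as assumed, equal variance cannot hold.

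**4. Actual size of an F-test on 0/1 data.** I enumerated every pair of responder counts for 9 per arm at a single visit. This is the simplest case, because the Update does not define the repeated-measures test.

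- 0/9 against 3/9: pooled variance 9·(1/3)(2/3)/16 = 0.125, standard error √(0.125·2/9) = 0.167, t = 0.333/0.167 = 2.00. The critical value on 16 df is 2.12, so this does not reject.
- 0/9 against 4/9: pooled variance 0.139, standard error 0.176, t = 2.53. This rejects.

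So when one arm has no responders, the other needs at least 4 of 9. At a common rate of 10%, P(0) = P(1) = 0.387, P(≥4) = 0.0083 and P(≥5) = 0.0009. The size is about 2·0.387·0.0083 + 2·0.387·0.0009 = 0.007. Full enumeration gives:

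| Common response rate | Actual size at nominal 5% |
|---|---|
| 10% | 0.7% |
| 20% | 3.5% |
| 30% | 5.5% |
| 50% | 5.0% |

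The test is miscalibrated, mostly on the conservative side. At the control rate that the plan assumes, it is far from 5%.

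**5. The estimate.** A repeated measures ANOVA returns F-tests for group, time and their interaction. None of these is the 6-month difference in proportions with its 95% interval, and the NNT in Statistical analysis is the reciprocal of that difference.

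**6. Power of the planned comparison in 18 patients**, at 50% against 10% and 9 per arm. Normal approximation without correction: Φ[(0.4·√9 − 1.270)/√0.34] = Φ(−0.12) = 45%. Fisher's exact test, by enumeration: 30%.

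**7. The cut-off.** Only a patient at exactly 50% is affected. An illustrative simulation of 7-day diary means, with assumed distributions, gave 48.2% responders under ≥50% and 47.0% under >50%, a shift of about 1 point.

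**The case against.** The strongest reply is one of scope. The Update describes a preliminary look at 18 patients. It does not amend Statistical analysis, which still fixes the binomial comparison at 6 months. This stands: neither the final analysis nor the sample size is touched.

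Second, Study endpoints already puts the pain-score change in the same paragraph as the primary outcome, and secondary outcomes begin only in the next. The Update's pairing may echo that layout rather than create a second primary outcome. This largely stands. A reader might infer a familywise error of 8 to 9% from two primary tests, but that assumes each has a true 5% level. At a 10% response rate the responder test has size 0.7%, so the total is at most 5.0 + 0.7 = 5.7%.

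Third, the change of inequality sign may be loose wording; the Discussion also writes it as a strict inequality when describing the earlier case series. This stands too, and the effect is small.

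Fourth, for individual pain reduction, repeated measures ANOVA is a usable method, though not the planned one. A reader might infer that it dilutes the treatment effect by averaging in visits before or around implantation. The document does not support that, because the Update names neither visits nor contrast, and the answer turns on both. Assume a 3-point benefit at 3 and 6 months and none at 2 weeks and 1 month, with SD 2, correlation 0.5 and 9 per arm. Simulated power is then about 48% for a group main effect over four post-baseline visits, 98% for group-by-time with baseline included, and 85% for the baseline-to-6-month change, against 91% for 6-month ANCOVA.

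None of these replies makes ANOVA suitable for the responder count or reconciles the Update with the Methods.

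**Conclusion.** The point holds for the preliminary analysis. The method named in the Update is unsuitable for the responder part of what it calls the primary outcome, and it does not deliver the planned 6-month risk difference. The size is a nominal 5% test with an actual level between 0.7% and 5.5% over response rates of 10 to 50%. That rests on an assumed 9 per arm and a single-visit F-test as a stand-in for the unspecified repeated-measures test. The error is mainly conservatism, not serious inflation.

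A reader might conclude that the trial's primary outcome has been replaced, or that the pain-score analysis loses power. The document supports neither. The two-part outcome and the strict inequality are wording conflicts to be reconciled. Severity: should-fix.

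**What to change.** In the Update, replace the repeated measures ANOVA sentence with:

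- **Responder outcome.** Proportion with ≥50% reduction in average NPRS at 6 months, by intention to treat, as the risk difference of Statistical analysis with a score or exact interval. The interval is an addition to the plan, made because the sample is small, and should be labelled so. If the Bayesian approach in the next sentence is kept, use a Bayesian binomial analogue of the same difference and say that it takes the place of the frequentist test for this look.
- **Pain change.** Report separately as the additional 6-month baseline-adjusted ANCOVA already planned, not as part of the primary outcome.
- **Wording.** Write ≥50% throughout and state the 6-month time point.

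The cost is wording and a small re-run, with no data beyond those already scheduled. A patient enrolled in November 2016 reaches 6 months in May 2017, so the report should state how many of the 18 have 6-month data. The drawback is low power, about 30 to 45% for 50% against 10% with 9 per arm, so the result should be presented as preliminary and a non-significant difference should not be read as absence of effect.

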## Abbreviations

BPI: Brief Pain Inventory
CMM: Conventional Medical Management
CPIP: Chronic Post-herniorrhaphy Inguinal Pain
DRG: Dorsal Root Ganglion
DSIS: Daily Sleep Inventory Score
ITT: Intention To Treat
NNT: Number Needed to Treat
NPRS: Numerical Pain Rating Score
PSIP: Post Surgical Inguinal Pain
SCS: Spinal Cord Stimulation
TENS: Transcutaneous Electrical Nerve Stimulation
TNS: Temporary Neuro Stimulation
